**Brazil**	
Fortaleza	3,580
Sobral	498
**Total Brazil**	**4,078**
**Nepal**	
Dhanusha	1,724
Mahottari	885
Sarlahi^b^	411
**Total Nepal**	**3,020**
**Bangladesh**	
Rangpur	1,734
Nilphamari	1,671
**Total Bangladesh**	**3,405**
**Study total**	**14,532**

Sources – National Health Information System on Notifiable Diseases (SINAN; Brazil); Primary Care Health Centres at sub-district level and district consolidation (India, Nepal, and Bangladesh)

^a^Fiscal year is from April 2015 to March 2021

^b^Sarlahi coverage is partial (9 out of 20 municipalities) due to SDR-PEP roll-out in other areas

The contacts who consent to participate in the trial will first be screened by the research staff for signs and symptoms of leprosy and tuberculosis (TB) and checked for eligibility criteria. Exclusion criteria for the administration of preventive treatment are refusal to provide informed consent, a history of liver, renal or cardiac disease or a known allergy to RMP and/or CLR. Contacts are also temporarily ineligible if: pregnant or breastfeeding, under the age of two years, received RMP for any reason in the last two years or using contraindicated medicines for non-chronic use. If these conditions change during the trial intake period, they may still be included in the study. In the presence of any possible signs of leprosy, the participant will be referred to the closest qualified health centre for confirmation of diagnosis. Those who are confirmed as a new leprosy case are subsequently requested to list their close contacts for enrolment in the study.

### Randomisation

The allocation of intervention and control arms in the countries has been done blindly using stratified randomisation. For each country, the randomisation unit has been determined via consultation with local government officials and project staff. This resulted in the use of territories/neighbourhoods in Brazil, blocks in India, municipalities in Nepal and unions in Bangladesh. These randomisation units were divided into two strata based on the number of clusters and the number of cases in clusters (based on geospatial analysis results with data from 2015–2020) followed by random sampling into intervention or control arms.

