### Study design

The study will use a cluster-randomised non-blinded controlled trial design with two arms to compare the effectiveness of three doses of RMP/CLR (the PEP++ regimen) with SDR-PEP in the prevention of leprosy disease among contacts of newly diagnosed leprosy patients. The randomisation units will sub-district divisions in each country context that will be randomly allocated to the two study arms.

All eligible leprosy patients in the districts will be asked to enumerate their close contacts. These individuals will subsequently be approached and enrolled in the study. Those contacts who provide informed consent are screened for signs of leprosy and tuberculosis and for inclusion eligibility. Contacts of leprosy patients living in the intervention arm receive the PEP++ regimen while those in the control arm receive SDR-PEP. All participants included in the study will be followed up two years after receiving the final dose of PEP++ or SDR-PEP.

The residences of the leprosy cases approached for the study will be geocoded in order to develop epidemiological maps that identify clusters of leprosy cases. After the regimen trial intake is concluded, blanket campaigns with SDR-PEP will be implemented in these clusters (high-risk areas) to reduce leprosy incidence at the population level. The study schedule is presented in Fig. 1. A checklist of Recommendations for Clinical Intervention Trials (SPIRIT) is also available (Supplementary file 1).

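### The area's arm is fixed and can be known before contacts are listed, consent and are screened, so the contact-level comparison is open to differential recruitment

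*Protocol article*

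**What the plan says.** All places are in the protocol article.

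- **Study design.** "The study will use a cluster-randomised non-blinded controlled trial design with two arms". Contacts' regimen is determined by the area of residence.
- **Randomisation.** "The allocation of intervention and control arms in the countries has been done blindly using stratified randomisation". On stratification: "These randomisation units were divided into two strata based on the number of clusters and the number of cases in clusters", using 2015–2020 data. The allocation is reported as completed. The abstract puts it in the future tense but also places it ahead of listing and enrolment.
- **Study design, on recruitment.** "All eligible leprosy patients in the districts will be asked to enumerate their close contacts", and then "These individuals will subsequently be approached and enrolled in the study". Both steps are still to come.
- **Participants.** Index cases come from programme registries and must have been detected in 2015 or later. A close contact is defined by an approximate number of hours per week over at least three months. Those who are listed and located are enrolled.
- **Participants, text after Table 1.** "The contacts who consent to participate in the trial will first be screened by the research staff for signs and symptoms of leprosy". One set of exclusion criteria covers both arms, including allergy to either drug.
- **Data collection.** A code linked to the index case is created first. The contact is then visited at home and asked for consent. Relationship to the index case is recorded on the registration form.

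**The concern.** Randomising areas balances areas. It does not balance the individuals recruited inside them once the arm can be known. In this trial several steps that involve judgement or choice decide who enters the contact cohort: whom the index case recalls and names (for diagnoses going back to 2015), whether that person meets an approximate definition, whether staff locate them, whether they agree, and whether staff see possible signs at screening. The two regimens ask different things of participants: three supervised two-drug doses against one single-drug dose. The document itself treats the acceptability of PEP++ compared with SDR-PEP as a secondary outcome (Table 3).

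The mix of contacts matters because the abstract and Background place household members and blood relatives at higher risk. If the share of such contacts among those recruited differs by arm, the arms start with different expected incidence, and the Cox and Poisson comparison would attribute that difference to the regimen. More participants would not remove it.

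**Working it through.** **1. Order of steps, set side by side.**

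| Step | Timing | Can the arm be known? |
|---|---|---|
| Draw of areas | Done | Draw was blind |
| Index case lists contacts | After | Yes: arm follows from area, trial is open |
| Staff locate contacts | After | Yes |
| Contact consents | After | Yes |
| Staff screen and check eligibility | After | Yes |

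The word blindly can apply only to the first row. The document does not say that index cases are told the regimen when they list contacts, and it does not say that they are kept from knowing it.

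**2. The plan's own figure.** The only related figure is the 202,360 contacts under Sample size. With 0.00146 against 0.00073, two-sided 0.05 and 90% power, a two-proportion calculation gives 43,132 per arm. Then 43,132 × 2 × 1.5 = 129,396, and 129,396 × 1.25 × 1.25 = 202,181, within 0.1% of 202,360. This point does not dispute that number.

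**3. What a difference in mix would do (all inputs assumed).** Let k be the risk of close (household or blood-related) contacts relative to others, p0 their share in the control arm and p1 their share in the PEP++ arm. With no drug effect, the rate ratio is

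(p1·k + 1 − p1) / (p0·k + 1 − p0).

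Take p0 = 0.50. The denominator is 1.5 for k = 2 and 2.0 for k = 3.

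| p1 | k = 2 | k = 3 |
|---|---|---|
| 0.45 | 1.45/1.5 = 0.97 | 1.9/2.0 = 0.95 |
| 0.40 | 1.40/1.5 = 0.93 | 1.8/2.0 = 0.90 |
| 0.30 | 1.30/1.5 = 0.87 | 1.6/2.0 = 0.80 |

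If the share rises instead, the bias reverses: 0.55 with k = 2 gives 1.55/1.5 = 1.03, and 0.70 with k = 3 gives 2.4/2.0 = 1.20.

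**4. What that would do to inference (illustration).** Reading each 25% correction as a proportion lost, the effective number per arm is 202,360 × 0.75 × 0.75 / 2 / 1.5 ≈ 37,942. The control rate is the stated 291/100,000 over two years. With no drug effect and a baseline risk 10% or 20% lower in the PEP++ contacts, the two-proportion test would favour PEP++ significantly with probability about 12% or 35%, against a nominal 2.5%. With a true rate ratio of 0.50, a 20% shift either way gives an apparent ratio of 0.50 × 0.80 = 0.40 or 0.50 × 1.20 = 0.60.

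**The case against.** The strongest reply is that there are partial safeguards and that the illustration has no empirical base. Index cases come from registries, contacts have a stated definition, everyone listed and located is to be enrolled, the linked code is created before the home visit at which consent is sought, and the exclusion criteria are the same in both arms. All of this is correct and narrows the opening. It does not control whom a patient names, who agrees, or how signs are judged at first screening. It is also true that the 50% share, the risk ratios of 2 and 3 and the gaps in share are assumptions. The Background and Discussion report that SDR-PEP works less well in close contacts, which is a difference in effect and supplies no baseline risk ratio. Against a planned 50% reduction, the milder cases are small. A full protocol or analysis plan may add safeguards; the point rests on the stated sequence, not on their absence here.

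Four stronger readings are tempting but not supported.

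- A reader might infer that the draw itself was unconcealed. The Randomisation section says the opposite.
- A reader might infer that a single consent covers screening and drug, so that anyone who declines the regimen is lost to both. The document does not say so. "Exclusion criteria for the administration of preventive treatment are refusal to provide informed consent" concerns treatment only, prophylaxis is offered to eligible participants, and Table 3 counts the share of eligible contacts who take all doses, which requires eligible non-takers in the data.
- A reader might infer that study staff alone remove prevalent cases. Possible signs lead to referral to a health centre, where the diagnosis is confirmed.
- A reader might extend the point to every primary outcome. The last row of Table 3 compares new-case and child-case detection per 1,000,000 population between areas, and that denominator does not depend on who is listed or consents.

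**Conclusion.** The point holds for the contact-level primary comparison only (second comparison under Sample size; first row of Table 3). The arm is fixed and can be known at every entry step after the draw, no described step conceals it, and area-level stratification cannot balance later recruitment. This is an exposure to bias, not a demonstrated bias: the document gives no information on its direction or size. Under the assumed shares and risk ratios the null rate ratio ranges from 0.97 to 0.80, and it exceeds 1 if the imbalance runs the other way. The imbalance arises before any dose, so analysing by assigned arm does not cure it. It merits action mainly because the protection is cheap.

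**What to change.** 1. Use the same listing procedure in both arms, and close each index case's contact list, with relationship, before any regimen information is given to the patient or the contacts.
2. At the same home visit, record leprosy screening and eligibility in REDCap before discussing the area's regimen. The common exclusion criteria allow eligibility to be completed without reference to the arm. The sponsor should check that the consent form, which is not shown, permits this order.
3. Adjust the Cox and Poisson contact comparison for relationship to the index case, which is already collected.
4. Report listed, located, consenting and eligible contacts by arm and relationship.

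If intake is already advanced, items 3 and 4 still apply.

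The cost is a changed form order and slightly more analysis, with the same staff and visits. Two limits remain: an area's arm may become known locally whatever the form order, and adjustment corrects only for the relationship recorded, not for unmeasured differences.

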### Sample size

The calculation of the sample size is based on the primary objective to find differences in new case detection rates (NCDR). The first is a difference in NCDR in the population in the intervention area after four years, compared to the baseline rate in 2019. The year 2019 is selected as the baseline to avoid any effect of the COVID-19 pandemic. The second is the difference in incidence rates in the contact groups between the close contacts who have received PEP++ and controls who have received SDR-PEP.

The sample size calculation for the difference in rates in the close contacts is based on the NCDR found in contacts in the COLEP trial sample. The NCDR in the SDR intervention group was 291/100,000 over 2 years, or an annual rate of 146/100,000. To reduce this rate by 50%, using a power of 90%, a significance level of 0.05, design effect of 1.5, correction for non-eligibility of 25% and loss to follow-up of 25%, we aimed to enrol 202,360 close contacts. This should result in giving PEP to at least 162,000 participants.

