### Data analysis

Data from the PEP++ trial will be analysed primarily through quantitative methods using descriptive analysis for all variables. Table 3 outlines the tools to be used to measure and analyse the study outcomes.

**Table 3 Tab3:** PEP++ project outcomes and statistical analysis plan

Objective	Outcome	Hypothesis	Outcome measure	Method of analysis
To provide evidence of the effectiveness of an enhanced post-exposure prophylaxis regimen (PEP++) compared to SDR-PEP	Primary: contacts diagnosed with leprosy	PEP++ offers a higher protection against leprosy disease manifestation than SDR-PEP	Number of persons with leprosy disease detected at 24 months after receiving prophylaxis	Descriptive statistics; Cox’ proportion hazards analysis and Poisson regression comparing rates between the intervention and control areas
To show the cost- benefit and acceptability of the enhanced chemoprophylaxis regimen	Secondary: Cost–benefit of the enhanced regimen compared with effectiveness of SDR-PEP	PEP++ is a cost-effective strategy in leprosy control and the increased effectiveness of the intervention will justify additional costs from multiple doses	Number of contacts screened, cases prevented, and disabilities avoided against operational costs and out-of-pocket expenses	Health economic evaluation
	Secondary: Acceptability of the enhanced regimen compared with SDR-PEP	The new regimen will be accepted by contacts and health professionals	Proportion of eligible close contacts who take all three doses; qualitative interview results indicating that PEP++ is acceptable	Descriptive statistics of contacts who took medication; qualitative content analysis of interviews; semi-structured interviews, FGDs
To provide evidence of increased transmission of *M. leprae* in cluster areas identified through GIS-based mapping compared to non-cluster areas	Secondary: Contacts diagnosed with leprosy in identified high-transmission clusters (2014–19 index cases)	Detection of new leprosy cases will be higher in the cluster areas than in non-cluster areas due to higher local transmission and relative risk	Rate ratios of all new leprosy cases and child cases in cluster areas as compared with non-cluster areas (as a result of intervention as well as passive cases); rate ratio	Poisson regression comparing rates between cluster and non-cluster areas

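### The contact sample size counts one year of leprosy risk per contact while the outcome covers two, so the stated 90% power understates what the enrolment target delivers

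*Protocol article*

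**What the plan says.** The protocol article, under Sample size, takes the control rate from the earlier SDR trial in contacts: "291/100,000 over 2 years, or an annual rate of 146/100,000. To reduce this rate by 50%, using a power of 90" per cent. The other inputs are "a significance level of 0.05", a design effect of 1.5, and corrections of 25% for non-eligibility and 25% for loss to follow-up. The result is an enrolment target of 202,360 close contacts, of whom at least 162,000 should receive prophylaxis.

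Under Study design, follow-up is stated as: "All participants included in the study will be followed up two years after receiving the final dose of PEP++ or SDR-PEP". In Table 3 (Data analysis), the outcome measure for the primary effectiveness objective is: "Number of persons with leprosy disease detected at 24 months after receiving prophylaxis". The Abstract and the Outcome measures section also place the assessment at two years.

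**The concern.** The section halves the two-year figure to an annual rate and sizes the trial on that. An annual rate is a sound input if each contact then contributes two person-years. If each contributes only one, half of the expected cases are left out and the required number of contacts roughly doubles.

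At stake is what the trial is said to be able to detect. The comparator is active, so a reduction smaller than 50% may well matter. The design effect of 1.5 is printed without an intracluster correlation or cluster size, although the randomised units range from neighbourhoods to blocks and municipalities. A reader who takes 90% for 50% at face value will misjudge how much clustering or recruitment shortfall the trial can absorb, and how to read a moderate or null result.

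**Working it through.** **Inputs.** From Sample size: control risk 0.00291 over two years, or 0.00146 per year; 50% reduction; power 90%; alpha 0.05; design effect (DE) 1.5; losses of 25% and 25%. Assumed, because not stated: two-sided test and 1:1 allocation.

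**Formula.** For two proportions with pooled variance and no continuity correction, per arm:

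n = [1.960·√(2p̄(1−p̄)) + 1.282·√(p1(1−p1) + p2(1−p2))]² / (p1−p2)², where p̄ = (p1+p2)/2.

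**1. Reproducing the plan's figures with one year of risk (0.00146 vs 0.00073).**
- n = 43,132 per arm; × 2 × 1.5 = 129,395
- × 1.25 = 161,744 (stated: 162,000; 0.16% below)
- × 1.25 = 202,180 (stated: 202,360; 0.09% below)

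A Poisson rate comparison with one person-year per contact gives 161,929 and then 202,412 (0.03% above). Both printed figures come out of a single chain.

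**2. Same calculation with the two-year risk (0.00291 vs 0.001455).**
- n = 21,615 per arm; × 2 × 1.5 = 64,846
- × 1.25 × 1.25 = 101,322 enrolled
- or / 0.75 / 0.75 = 115,282 enrolled

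**3. What 202,360 delivers at the two-year risk.** The answer depends on how the losses are applied, so both are shown.

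| | Losses as × 0.75 × 0.75 | Losses as / 1.25 / 1.25 |
|---|---|---|
| Evaluable contacts | 113,828 | 129,510 |
| Per arm | 56,914 | 64,755 |
| Per arm after DE 1.5 | 37,942 | 43,170 |
| Power for a 50% reduction | 99.0% | 99.6% |
| Reduction detectable at 90% power | 39% | 37% |
| Largest DE with 90% power for 50% | 56,914 / 21,615 = 2.6 | 64,755 / 21,615 = 3.0 |
| Expected cases, SDR-PEP vs PEP++ | 166 vs 83 | 188 vs 94 |

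**4. If the one-year rate was a deliberate margin.** Treat 146 per 100,000 as the risk over the full two years. Power is then 90% with losses as / 1.25 / 1.25, but 86% when 25% are truly lost at each step. With true losses, the two-year control risk covered at 90% power is about 146 × 43,132 / 37,942 = 166 per 100,000.

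**5. A separate matter.** The chain that matches the printed figures inflates by 1.25 twice. Losing 25% at each step calls for division by 0.75 twice, which at the one-year rate gives 230,036. This runs in the opposite direction to the issue above and accounts for the ranges in step 3.

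**The case against.** The strongest reply is that this is a safety margin: borrowed rates often prove too high, design effects too low, and a trial larger than its formula requires harms no inference. The surplus could indeed be used up. At the two-year risk with true 25% losses, power for a 50% reduction falls to 86% at a design effect of 3 and 75% at 4. But the section lists its allowances (design effect, non-eligibility, loss to follow-up), and a halved control risk is not among them. The full protocol may give a reason that the article omits; the printed inputs and the printed outcome window would still not fit together.

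A second reply is that one person-year per contact is inferred, since no formula is printed. That is fair, and other routes come close. A one-sided, continuity-corrected version gives 201,835, but it also uses 146 and misses the 162,000 step. The two-year risk gives 162,120 and 202,650 if the two-arm total is doubled once more, but nothing explains that doubling, and the target would still be twice what the inputs require. The conclusion is the same on either route.

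A reader might infer from the mismatch that the trial is underpowered. The documents support the opposite. A reader might also infer that enrolment should be cut to 101,000 to 115,000. That does not follow: the design effect is unsupported in the text, and the Sample size section names a second aim (population detection against 2019) that the contact calculation does not size.

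**Conclusion.** The point holds. The stated 90% power for a 50% reduction does not describe a trial that follows contacts for two years. The plan counts about half the risk that its own source gives for that window, and the discrepancy is conservative. With 202,360 enrolled and a design effect of 1.5, power is about 99.0% to 99.6%. The assumptions are two-sided 0.05, 1:1 allocation, and the plan's own control rate and design effect; the ranges reflect the two ways of applying the losses. The text does not show whether the one-year rate was a slip or an unstated margin. No estimate or analysis is affected, only the claim about what the trial can detect.

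**What to change.** In Sample size, recompute on the two-year risk (291 vs 145.5 per 100,000) or on two person-years per contact, keep 202,360, and restate the power: about 99% for a 50% reduction at design effect 1.5, or 90% for a reduction of about 37% to 39%, or 90% for 50% up to a design effect of about 2.6 to 3.0. Choose one loss convention and give the single figures that go with it. State the sidedness and the allocation ratio.

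If the annual rate was meant as a margin, say so and give the two-year control risk covered at 90% power: about 166 per 100,000 with true 25% losses at each step. The figure of 146 per 100,000 is right only under the × 1.25 inflation.

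Deal with × 1.25 versus / 0.75 in its own sentence, so that the two issues are not netted against each other. The cost is a few sentences of wording; enrolment, conduct and analysis do not change.

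### The enrolment target, the 25% non-eligibility and the expected number on PEP do not fit together: 202,360 enrolled gives 151,770 on PEP, not 162,000

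*Protocol article*

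**What the plan says.** All the planning figures stand in one paragraph of the protocol article, under Sample size.

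- Control rate: "The NCDR in the SDR intervention group was 291/100,000 over 2 years, or an annual rate of 146/100,000".
- Target effect: a 50% reduction of that rate, with 90% power, "a significance level of 0.05" and a "design effect of 1.5".
- Losses and target: "correction for non-eligibility of 25% and loss to follow-up of 25%, we aimed to enrol 202,360 close contacts".
- Yield: "This should result in giving PEP to at least 162,000 participants".

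The paragraph does not give the inflation formula, the sidedness of the test, the allocation ratio, or whether the one-year or the two-year risk entered the calculation. It states no evaluable number. Elsewhere, Study design sets follow-up at two years after the last dose, Outcome measures places the primary outcome at the two-year follow-up, and Table 3 counts cases at 24 months.

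**The concern.** If a quarter of those enrolled are not eligible, three quarters can be treated. Three quarters of 202,360 is well short of 162,000, so the target, the non-eligibility percentage and the expected number on PEP cannot all be right.

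Two things are at stake. The first is the treated number. A team that tracks progress against 162,000 would see a shortfall of about 6% even if every planning assumption held, and a reader cannot tell whether 20% or 25% non-eligibility was planned. The second is the link between the stated losses and the stated 90% power. If the losses were under-corrected, the power quoted does not follow from the inputs quoted.

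**Working it through.** **Inputs from the Sample size section.** Annual rate 146 per 100,000, halved to 73; two-year rate 291 per 100,000, halved to 145.5; power 90%; alpha 0.05; design effect 1.5; losses 25% and 25%. **Assumed, because not stated:** two-sided test, 1:1 allocation.

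**Step 1. The contradiction, which needs none of these assumptions.**
- Treated at 25% non-eligibility: 202,360 × 0.75 = 151,770.
- Shortfall: 162,000 − 151,770 = 10,230, or 6.3% of 162,000.
- Share implied by the printed pair: 162,000 / 202,360 = 80.1%, a loss of about 20%.
- Enrolment needed for 162,000 treated at 25%: 162,000 / 0.75 = 216,000.

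**Step 2. Reproducing 202,360.** Comparison of two proportions:

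n per arm = [z₀.₉₇₅ √(2p̄(1−p̄)) + z₀.₉₀ √(p₁(1−p₁) + p₂(1−p₂))]² / (p₁−p₂)²

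With p₁ = 0.00146, p₂ = 0.00073 and p̄ = 0.001095, n = 43,132 per arm.
- Two arms and design effect: 43,132 × 2 × 1.5 = 129,396.
- Multiplied by 1.25 once: 161,745, against 162,000 printed.
- Multiplied by 1.25 again: 202,181, against 202,360 printed (0.1% apart). The Poisson variance form gives 202,412.
- Working back from the printed target: 202,360 / 1.25 = 161,888, which rounds to 162,000; 161,888 / 1.25 = 129,510.

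Multiplying by 1.25 offsets a loss of 1 − 1/1.25 = 20%. Offsetting 25% requires division by 0.75.

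**Step 3. Other routes.** Dividing by 0.75 twice gives 129,396 / 0.5625 = about 230,040 enrolled and 129,396 / 0.75 = about 172,530 on PEP, matching neither printed figure. A one-sided, continuity-corrected calculation divided by 0.75 twice gives 201,835 enrolled, close to the target, but then 201,835 × 0.75 = 151,376 on PEP. An events formula at 145.5 per 100,000, with division by 0.75 for follow-up and multiplication by 1.25 for eligibility, gives 161,283 and 201,604. That fit is looser, and it still has 1.25 at the eligibility step. Of the routes tried, multiplying by 1.25 twice fits the pair most closely.

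**Step 4. What remains after both stated losses.** 202,360 × 0.75 × 0.75 = 113,828 (rounded up). Per arm, after the design effect: 113,828 / 2 / 1.5 = 37,943.

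**Step 5. Power with 113,828 followed up** (approximately z = difference / SE, power = Φ(z − 1.96)).

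| Risk used | Difference | SE | z | Power, two-sided |
|---|---|---|---|---|
| Annual, 146 vs 73 per 100,000 | 0.00073 | 0.000240 | 3.04 | 86.0% |
| Two-year, 291 vs 145.5 per 100,000 | 0.001455 | 0.000339 | 4.29 | 99.0% |

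On the annual rate, one-sided power would be 91.9%. If 162,000 did receive PEP and 25% of them were then lost, 121,500 would remain, with two-sided power of 88.1%. On the two-year rate, 90% power with division by 0.75 twice needs only about 115,285 enrolled.

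**The case against.** The strongest objection concerns power. A reader might infer from Step 5 that the trial is underpowered. The document does not support that. The 86% arises only when a one-year rate is treated as the whole risk over a two-year follow-up, with a two-sided test and equal allocation, neither of which is stated. The plan also gives the two-year rate and measures its outcome at 24 months. On that rate the same contacts give about 99%, and the target far exceeds what is needed. Using the annual rate more than offsets the under-correction for losses. This objection stands in full.

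Second, the 25% correction could be read as a 25% uplift. The printed pair then agrees and only the label is loose. This is probably how the figures arose, but the label gives non-eligibility as 25%, and a 25% uplift does not cover that.

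Third, the Participants section lets temporarily ineligible contacts join if their condition changes during intake, so treated numbers could exceed three quarters of those enrolled. That is fair for the field, but the calculation states a single 25% and no allowance for recovery.

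Fourth, a reader might take 129,510 evaluable, or losses of 20% and 20%, as the plan's own assumptions. Both are inferred by working backwards and appear nowhere in the document. The only shortfall against a printed target is in the number on PEP.

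**Conclusion.** The Sample size paragraph contradicts itself. At the stated 25% non-eligibility, 202,360 enrolled gives 151,770 on PEP, about 10,200 (6%) below a figure given as a minimum. This rests on one multiplication and on the ordinary reading of non-eligibility as a share of those enrolled.

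The likely cause, multiplication by 1.25 where division by 0.75 was needed, is an inference, though a well-supported one. Its effect on power is conditional: about 86% instead of 90% on the annual rate that reproduces the target (two-sided, 1:1), and about 99% on the two-year rate that matches the outcome. The error therefore lies in the published derivation and the treated number. It does not show that the trial enrols too few contacts.

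**What to change.** Correct the Sample size paragraph in one of two ways, with the enrolment target unchanged.

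- Keep 25% and 25%, and restate the yield as 151,770 on PEP and about 113,800 evaluable.
- If 20% and 20% was intended, say so. Then 202,360 × 0.80 = 161,888 on PEP and × 0.80 again = 129,510 evaluable, and the printed pair agrees after rounding.

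In either case, state whether the one-year or the two-year risk was used, the sidedness of the test, how the losses were applied, and the resulting power. At 25%/25% on the two-year risk that is about 99% (two-sided, 1:1). The 86% should not be printed as the power of the trial, because it belongs to the annual-rate basis only. The cost is a few sentences of text, with no extra participants.
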